### 2.7. Sample Size

Reduction in PE will be considered the primary outcome variable, and an estimate of the mean difference in PE reduction will be used to calculate the sample size. The primary acceptance criterion will be the PE effect of the evaluated medical devices showing at least a moderate effect of 20%.

To show a reduction in PE from 20% to 12% (with alpha = 5%, beta = 80%), coefficient of intraclass correlation of 0.03 and in a unilateral proportion test, we initially calculated 440 subjects per group. Assuming a potential dropout rate of 10%, 880 participants were determined as the target for patient inclusion.

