### 2.8. Recruitment

OP-PE trial will recruit 55 pregnant woman from each of the 16 clinical sites for a total of 880 subjects.

To identify participants, at the first visit for a pregnancy diagnosis, the physician will suggest that women who are less than 12 weeks pregnant, between the ages of 18 and 35, and who have never been pregnant before, participate in the study. If she responds positively, she will receive a trial information sheet and a consent form, and an inclusion visit will be scheduled by a qualified dental personnel. The total number of patients screened and recruited will be tracked. Patient volunteers will receive financial compensation.

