#### 2.10.3. Statistical Methods

The final analysis of the data will be based on intention-to-treat and will be performed with the STATA MP 16.0 software (College Station, TX 77845, USA). All principal statistical analyses will be based on the clusters as allocated in the randomization [36]. Intention-to-treat analyses will be performed on the imputed data from all patients using multiple imputation by chained equations, based on a Monte Carlo–Markov chain algorithm under missing at random data hypothesis. Unilateral analysis to study the superiority of intervention over control group will be programmed. Data entry and preliminary checks for error and internal validity will be carried out at each study site, with corresponding statistical analyses conducted at a central level. A series of explanatory analyses will also be conducted in which clinics and/or individuals deviating from the protocol will be excluded. Additionally, per-protocol analysis using the same methodology as the intention-to-treat analyses will be performed based on participants with a complete set of outcome data at endpoint.

The main analytical technique used to assess the effect of intervention on the primary outcome will be an application of the Mantel–Haenszel test adapted to the cluster randomization design. Baseline tables will be created comparing the intervention groups with respect to both cluster-level and individual-level risk factors. 

Groups will be compared as at randomization. The primary endpoint will be estimated by the Kaplan–Meier method (survival analysis) and comparison of the different groups by the Log Rank test (*p* < 0.05). A multivariate analysis by a Cox regression model will be used to explore the relationship between the risk function associated with PE and the intervention after adjustment for site, amenorrhea at inclusion, gestational age, maternal age, and periodontal parameters at inclusion. Continuous outcome variables will be analyzed using mixed model regression, with the clinic status treated as a random effect. Analyses will also be conducted to explore the possibility of an interaction effect between intervention and clinic size. All statistical analyses performed will account for the within-clinic correlation that would invalidate the application of standard statistical methods. The results will be communicated according to CONSORT guidelines.

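### 440 women per group does not allow for the stated ICC of 0.03: 16 clinics of 55 give about 60–64% power for 20% versus 12%, not 80%.

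*Protocol article*

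**What the plan says.** Section 2.7 of the protocol article (Sample Size) sets the target as a fall in pre-eclampsia from 20% to 12%. The error rates are given as "with alpha = 5%, beta = 80"%, where the second figure makes sense only as power. The test is described as "in a unilateral proportion test", and section 2.10.3 is consistent with that: "Unilateral analysis to study the superiority of intervention over control group will be programmed". The stated outcome of the calculation is "coefficient of intraclass correlation of 0.03 and in a unilateral proportion test, we initially calculated 440 subjects per group". Section 2.7 gives neither a cluster size nor a design effect.

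Section 2.8 supplies the cluster size: "OP-PE trial will recruit 55 pregnant woman from each of the 16 clinical sites for a total of 880 subjects". Sections 2.1 and 2.9.1 make the antenatal clinic the unit of randomisation, allocated 1:1, which puts 8 clinics in each arm.

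**The concern.** Section 2.7 presents 440 per group as a figure that already takes the intraclass correlation into account. With 55 women per clinic, even an ICC of 0.03 inflates the variance more than two and a half times, and 440 looks too small to have absorbed that.

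The figure underlies the power claim for the primary outcome. Section 2.10.3 says that all analyses will account for within-clinic correlation, so the analysis will pay a penalty that the sample size did not allow for. If power is really near 60%, a non-significant result says much less about a fall from 20% to 12% than the protocol implies.

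**Working it through.** **Inputs.** All come from the protocol article.

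- Control rate 0.20, intervention rate 0.12, one-sided alpha 0.05, power 0.80, ICC 0.03, 440 per group (section 2.7)
- 16 sites of 55 women (section 2.8)
- Clinics randomised 1:1 (sections 2.1 and 2.9.1), hence 8 per arm and 8 × 55 = 440

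**Step 1. Individually randomised size.** With p̄ = 0.16, the pooled-variance formula is

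n = [z₀.₉₅ √(2p̄(1 − p̄)) + z₀.₈₀ √(p₁(1 − p₁) + p₂(1 − p₂))]² / (p₁ − p₂)²

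= [1.645 × √0.2688 + 0.842 × √0.2656]² / 0.08² = 258.6, so 259 per arm.

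**Step 2. Allow for clustering.** The design effect is 1 + (55 − 1) × 0.03 = 2.62. The requirement is 258.6 × 2.62 = 677.6, so 678 per arm (about 1,356 in total). The plan has 440, which is 440/678 = 65% of that.

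**Step 3. Try to reproduce 440.** Dividing, 440/258.6 = 1.70. A design effect of 1.70 needs one of the following:

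- clusters of 1 + 0.70/0.03 ≈ 24 women with ICC 0.03, or
- an ICC of 0.70/54 ≈ 0.013 with 55 women per clinic.

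Neither figure is in the document. The only other cluster figure, the ability to include at least 150 women per clinic (section 2.3.1), would make the design effect larger. If 440 were meant to include the 10% dropout, 396 would be evaluable and the implied design effect would be 396/258.6 = 1.53, further still from 2.62. Unpooled variance, continuity correction, two-sided testing and 90% power do not give 440 either once the factor of 2.62 is applied.

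The figure does coincide with the pooled-variance size for two-sided 5% and 90% power with no clustering (439.2, rounded up to 440). The document does not say that this is its origin, and nothing below depends on it.

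**Step 4. Power of the planned design.** The standard error of the difference is √((0.16 + 0.1056) × 2.62/440) = 0.0398, and 0.08/0.0398 = 2.01.

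| Method | Power, 20% vs 12%, one-sided 5% |
|---|---|
| Normal approximation, Φ(2.01 − 1.645) | 64.3% (63.9% with pooled null variance) |
| Noncentral t, 14 df (16 clinics less 2) | 60.6% |
| Beta-binomial simulation, 40,000 runs | about 61% |

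**Step 5. Effect detectable with 80% power.** Solving for the intervention rate with 8 clinics of 55 per arm gives 10.4% (normal) or 9.9% (t). That is a fall from 20% to about 10%.

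**Step 6. With the protocol's own 10% dropout.** The target of 880 equals 2 × 440, so nothing was added for dropout. With 49.5 evaluable women per clinic the design effect is 1 + 48.5 × 0.03 = 2.455. Power is then 62–63% (normal) or 59.1% (t), and the detectable rate is 10.2% or 9.7%.

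**The case against.** The strongest objection is that section 2.8 speaks of clinical sites while the randomised unit is the clinic, and section 2.9.1 stratifies by study site as well as by clinic characteristics, as if the two differed. With two clinics per site there would be 32 clusters of 27.5 women. The design effect would be 1 + 26.5 × 0.03 = 1.795 and power 78% (normal) or 77% (t), close to the stated 80%.

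The document does not support that reading. Nowhere does it place two clinics in a site, and section 2.9.1 sends the allocation to the investigator of the selected site, which treats the site as the allocated unit. Even on that reading power stays below 80%, and after 10% dropout it is 75–76%. What stands is that equating site with clinic is an assumption and should be declared as one.

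Two smaller points also stand. A range of 60–64% assumes that all 880 women are evaluable; 10% loss takes it to 59–63%, though multiple imputation may recover part of that. And rewording the power statement leaves the trial as small as it was. A sponsor who wants to keep the 80% claim would have to add clinics.

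**Conclusion.** The stated 80% power is wrong on the protocol's own inputs. With ICC 0.03 and 55 women per clinic the requirement is 678 per group, not 440. The planned 8 + 8 clinics give about 60–64% power for 20% versus 12%, a type II error of 36–39% where 20% is claimed.

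This assumes that the 16 sites are the randomised clinics, that clinics are of equal size, that the 80% printed as beta means power, and that stratification brings no gain. Unequal clinic sizes would lower power further. No reading of the document that was tried restores 80%. The statement must be corrected, and confidence in this is high.

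**What to change.** If 16 clinics of 55 is what is feasible, keep it and rewrite the power statement in section 2.7, with matching text in the SAP. The revised statement should:

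- say that the 16 sites are the randomised clinics, and show the design effect, 1 + 54 × 0.03 = 2.62;
- give power of about 60–64% for 20% versus 12% at one-sided 5%, or 59–63% if 10% of women are not evaluable;
- state that the trial has 80% power for a fall from 20% to about 10%;
- label the 80% as power rather than beta.

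The cost is wording and a less favourable power figure; no extra participants are needed.

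The alternative is to keep the 80% claim and add clinics. With 10% dropout this takes 13 clinics of 55 per arm by the normal approximation (80.5%; 2 × 13 × 55 = 1,430 women) or 14 per arm with a t reference (81.4%; 2 × 14 × 55 = 1,540 women). Enlarging the existing clinics is not a practical route: with 8 per arm, about 1,090 women per clinic would be needed for 80% by the normal approximation.

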## 2. Material and Methods

### 2.1. Trial Design

This study protocol is reported according to the Standard Protocol Items: Recommendations for Interventional Trials (SPIRIT) guidelines [29]. This trial is designed as a two-arm, parallel, cluster randomized controlled trial with antenatal obstetric clinic as the unit of randomization and an allocation ratio of 1:1 (Figure 1). 

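### The 10% dropout allowance is announced but adds nobody: 880 is exactly twice 440, so 10% loss leaves 396 women per group

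*Protocol article*

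**What the plan says.** Section 2.7 (Sample Size) takes a fall in pre-eclampsia from 20% to 12%, a one-sided 5% test, 80% power (printed as a beta of 80%) and a "coefficient of intraclass correlation of 0.03". From these, it says, "we initially calculated 440 subjects per group". The next sentence brings in attrition: "Assuming a potential dropout rate of 10%, 880 participants were determined as the target for patient inclusion".

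Section 2.8 (Recruitment) repeats the total as the number to be enrolled: "OP-PE trial will recruit 55 pregnant woman from each of the 16 clinical sites for a total of 880 subjects". Section 2.1 sets two arms with "an allocation ratio of 1:1". Section 2.9.1 stops inclusion at each site once its planned number is reached. The article gives no larger enrolment figure and does not say that 440 already contains an allowance for loss.

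**The concern.** The order of the two sentences tells the reader that 440 per group is the requirement before attrition and that 880 is what results once 10% loss has been allowed for. The two numbers cannot have that relation, because 880 is simply two groups of 440.

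A reader would conclude that about 440 women per group will still have a known outcome after 10% loss. The plan as written delivers about 396, so the recruitment target does not give the protection claimed for it, and any power quoted at 440 is quoted at the wrong number.

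**Working it through.** **Inputs.** From section 2.7: 440 per group; dropout 10%; inclusion target 880; rates 20% and 12%; one-sided α = 5%; power 80%; ICC 0.03. From section 2.8: 16 clinics of 55. From section 2.1: 1:1 allocation, taken here as 8 clinics per arm.

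**1. The plan's own total.**
- 2 × 440 = 880 and 16 × 55 = 880. Both equal the stated target, so the factor applied for dropout is 880/(2 × 440) = 1.00.

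**2. What a 10% allowance on 440 would give.** Required enrolment = n/(1 − d).
- 440/0.90 = 488.9, so 489 per group and 978 in total.
- 978 − 880 = 98 women.
- Over 16 equal clinics, 978/16 = 61.1. Rounding up to 62 per clinic gives 992.

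**3. What 880 leaves after 10% loss.**
- 880 × 0.90 = 792, or 396 per group. This is 44 fewer than 440.
- 396/8 = 49.5 per clinic.

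**4. Effect on power.** Design effect DE = 1 + (m − 1) × ICC. Standard error of the difference = √{[0.20 × 0.80 + 0.12 × 0.88] × DE/n} = √(0.2656 × DE/n). Power comes from 0.08/SE, one-sided 5%, with either a normal reference or a noncentral t with 16 − 2 = 14 degrees of freedom.

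| Women per group | m per clinic | DE | 0.08/SE | Power, normal | Power, t (14 df) |
|---|---|---|---|---|---|
| 440 (no loss) | 55 | 2.62 | 2.01 | 64.3% | 60.6% |
| 396 (10% loss) | 49.5 | 2.455 | 1.97 | 62.8% | 59.1% |
| 489 | 61.1 | 2.80 | 2.05 | 65.7% | 62.0% |

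The loss costs about 1.5 points. A pooled variance under the null gives nearly the same (63.9% and 62.4% for the first two rows, normal reference). The cost is small because the number of clinics is fixed and clustering dominates the variance.

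**5. Does 440 itself reproduce?** This matters because 440 might already include dropout.
- One-sided 5%, 80% power, 20% versus 12%, no clustering: 259 per group (284 with continuity correction).
- With DE 2.62: 259 × 2.62 = 679 per group before dropout, and 678.6/0.9 = 754 after.
- Two-sided 5%, 90% power, no clustering, no dropout: exactly 440.
- One-sided 80% power with about 24 women per clinic: about 438. The article gives no such cluster size.

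The stated inputs with 55 per clinic give neither 440 nor 396. None of the variants tried with those inputs and that cluster size (one- or two-sided, 80% or 90% power, with or without continuity correction, pooled, unpooled or arcsine) points to 396 as a pre-dropout requirement. Steps 1 to 3 do not depend on where 440 came from.

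**The case against.** The best defence is that 440 already contains the allowance. The arithmetic permits it, since 396/0.9 = 440 exactly, and 880 is described as an inclusion target. On that reading the plan does cover dropout and only the wording is loose. The wording is against it, though: 440 is presented as the initial result, attrition is introduced afterwards, and 396 appears nowhere. Even so, the sentence would need correcting, because the requirement would then be 396 and not 440. The number left after 10% loss is 396 under either reading.

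A second objection is that 396 overstates the damage. Section 2.10.3 keeps all randomised women through multiple imputation, women lost to follow-up contribute time to the Kaplan–Meier and Cox analyses until censoring, and section 2.6.4 takes pre-eclampsia from medical records, so a woman who stops attending visits may still have a known outcome. This stands as a qualification: 396 applies if every dropout lacks an outcome. But imputation under missing at random keeps the denominator without restoring the lost information, and none of this supplies the allowance that section 2.7 claims.

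Third, the shortfall of 98 women takes 440 as a valid requirement, which step 5 does not support. That is fair. Raising enrolment to 489 per group would bring power only to about 62–66%, so 978 should not be read as the number that restores 80%.

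**Conclusion.** The statement in section 2.7 is wrong as written. The 10% allowance adds no women: 880 is the uninflated total, 98 short of what 10% loss on 440 per group would require, and it leaves about 396 per group with an observed outcome. This assumes loss falls equally on the two arms and that dropouts have no recorded outcome.

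By itself the slip costs about 1.5 percentage points of power, assuming ICC 0.03, equal clinics and 8 clinics per arm. The remaining gap, from 61–64% without any loss to the stated 80%, belongs to the missing design effect, which is a separate fault and should not be charged to dropout. The point should be corrected, but it does not by itself decide whether the trial is adequately sized.

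**What to change.** In section 2.7, state that 880 is the number enrolled, that 10% loss is expected to leave about 396 women per group with an observed outcome (49 to 50 per clinic), and quote power at that number with the ICC and cluster size used. If 440 was intended to include dropout, give 396 as the requirement and no longer present 440 as the initial calculation.

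The dropout correction needs only changed wording and one recalculated figure, with no extra recruitment. The quoted power will be well below 80%, almost entirely because of the design effect, so 440 and the dropout step are best rebuilt together.

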### 2.8. Recruitment

OP-PE trial will recruit 55 pregnant woman from each of the 16 clinical sites for a total of 880 subjects.

To identify participants, at the first visit for a pregnancy diagnosis, the physician will suggest that women who are less than 12 weeks pregnant, between the ages of 18 and 35, and who have never been pregnant before, participate in the study. If she responds positively, she will receive a trial information sheet and a consent form, and an inclusion visit will be scheduled by a qualified dental personnel. The total number of patients screened and recruited will be tracked. Patient volunteers will receive financial compensation.

### 2.9. Assignment of Interventions

#### 2.9.1. Allocation

In this conventional (parallel) cluster randomized trial, antenatal care clinics will be randomized to either the intervention or control arm at the start of the trial and remain in that arm for the duration of the study [35]. The allocation schedule for randomly assigning clinics will be computer generated, and stratified by study site and clinic characteristics at a central location (UR4129 Research Unit, University Lyon, France) by the study officer of the research using e-CRF Voozalyon 1.3 (Voozanoo, Caluire, France). Once the local investigators are operational for the implementation of the training seminars for the clinic staff, the treatment allocation will be sent by email by the study officer to the principal investigator of the selected site. Eligible adults per site will be included in the study in the order of inclusion until the number of subjects per site specified in the protocol is reached.

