#### 2.3.2. Exclusion Criteria

The exclusion criteria will be pregnant women with: (i) fetal distress, (ii) congenital uterine and vaginal abnormalities, (iii) infectious or systemic diseases such as HIV, tuberculosis, candidiasis, cancers, hemopathies, (iii) premature termination of pregnancy for medical reasons, (iv) periodontal lesions of stage II, III, IV (i.e., PD ≥ 4 mm, and/or CAL ≥ 4 mm), generalized (>30% of sites), (v) history or treatment of PD, (vi) a course of dental or orthodontic treatment, (vii) absence of the 4 premolar–molar pairs, (viii) less than 20 natural teeth, excluding third molars, (ix) medication affecting the gum and/or oral mucosa, (x) regularly using interdental brushes and/or dental floss and/or mouthwash, and (xi) unable to answer questions or non-cooperative.

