#### 2.9.2. Blinding

There will be a separation between the assignment generator and those carrying out the assignment. Implementation of the intervention will be performed by personnel not involved in the data collection. Clinicians, clinical research associates, and statisticians will be blinded regarding the group category at the time of the evaluation and analysis. Identification codes will be retained by the study monitor and will not be opened until the end of the study.

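### Clinic allocation is disclosed to the site before women are invited, as the text implies, and nothing masks the inviters, requires consecutive approach or adjusts the main test for individual risk

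*Protocol article*

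**What the plan says.** **Randomisation and disclosure (2.9.1 Allocation).** The unit is the clinic: "antenatal care clinics will be randomized to either the intervention or control arm at the start of the trial and remain in that arm". Disclosure is tied to training. "Once the local investigators are operational for the implementation of the training seminars for the clinic staff", the arm goes out: "the treatment allocation will be sent by email by the study officer to the principal investigator of the selected site". The next sentence turns to enrolment: "Eligible adults per site will be included in the study in the order of inclusion until the number of subjects per site" fixed by the protocol is reached.

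**Invitation (2.8 Recruitment).** The first approach is made in the clinic: "at the first visit for a pregnancy diagnosis, the physician will suggest that women who are less than 12 weeks pregnant", aged 18 to 35 and never pregnant before, take part. A woman who agrees receives an information sheet and a consent form, and dental personnel schedule the inclusion visit. Numbers screened and recruited are tracked. The quota is 55 women in each of 16 sites.

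**Consent (2.6.2 and Table 1).** The text places signature at the inclusion visit, T1. Table 1 marks consent at T0.

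**Discretion (2.3.2 Exclusion Criteria).** One exclusion is a matter of judgement: "unable to answer questions or non-cooperative".

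**Blinding (2.9.2).** Clinicians, research associates and statisticians are blinded when they evaluate and analyse. Also, "Implementation of the intervention will be performed by personnel not involved in the data collection". Recruitment is not mentioned.

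**Analysis (2.10.3 Statistical Methods).** The main technique for the primary outcome is a Mantel–Haenszel test adapted to cluster randomisation. Baseline tables will compare the arms on cluster-level and individual-level risk factors. A Cox model adjusts for site, amenorrhea at inclusion, gestational age, maternal age and periodontal parameters.

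**The concern.** Randomising clinics balances the clinics, in expectation. It does not balance the women enrolled if they enter after the arm is fixed and may be known to the people who approach them. A physician in an intervention clinic may, without intending it, favour women who seem likely to keep up daily interdental brushing. A judgement about cooperativeness can also be applied differently where there is a regimen to cooperate with. Any such difference acts at entry, so intention-to-treat analysis does not correct it, and allowing for within-clinic correlation corrects the standard error but not the bias.

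What is at stake is the comparability of the arms on PE risk. The Introduction names obesity, chronic hypertension, metabolic or cardiovascular risks and severe anemia as the highest risk factors. None of these is in the Cox adjustment, and none is said to enter the main test.

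**Working it through.** The plan gives no figure on this point to reproduce. The check has two parts: the sequence of events, and an illustration of what an imbalance would do.

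**1. Sequence**

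| Step | Where | What is fixed |
|---|---|---|
| Arm assigned to clinic | 2.9.1 | Start of trial |
| Arm disclosed | 2.9.1 | To the site principal investigator, when staff training is ready |
| Women included up to quota | 2.9.1, next sentence | Date not given; the order of the text implies after disclosure |
| Women invited | 2.8 | By the clinic physician at the first pregnancy visit |
| Consent signed | 2.6.2 / Table 1 | T1 / T0 |
| Blinding | 2.9.2 | Evaluation and analysis only |

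The statement that "Eligible adults per site will be included in the study in the order of inclusion" orders the women who were included. It does not say that each eligible woman must be approached.

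**2. Room to select**

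Section 2.3.1 requires that a clinic be able to include at least 150 new pregnant women in no more than 6 months. The quota is 55, and 55/150 = 37%. The quota therefore need not exhaust the available women. Eligibility and refusal rates are not given, so how much room remains is unknown.

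**3. Illustration of size**

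Inputs from the documents (2.7 and 2.8): control risk 20%, one-sided 5% test, intraclass correlation 0.03, 55 women per clinic, 440 per arm.

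Assumed, not from the documents: no true effect, and a risk factor with relative risk k carried by 30% of control enrolees and 20% of intervention enrolees.

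- Design effect: 1 + (55 − 1) × 0.03 = 2.62. Effective size per arm: 440/2.62 = 167.9.
- Risk without the factor: b = 0.20/(1 + 0.30(k − 1)).
- Intervention risk under no effect: p = b(1 + 0.20(k − 1)).
- Standard error: √[(0.20 × 0.80 + p(1 − p))/167.9].
- One-sided error: 1 − Φ(1.645 − (0.20 − p)/SE).

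| k | b | p | Spurious difference | SE | Error (normal) |
|---|---|---|---|---|---|
| 1.5 | 0.1739 | 0.1913 | 0.9 points | 0.0433 | 7.4% |
| 2 | 0.1538 | 0.1846 | 1.5 points | 0.0430 | 9.9% |
| 3 | 0.1250 | 0.1750 | 2.5 points | 0.0426 | 14.5% |

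With a t distribution on 14 degrees of freedom (16 clinics minus 2), the figures for k = 2 and k = 3 are 9.6% and 13.9%. With a 20-point gap (30% against 10%), the normal figures for k = 1.5, 2 and 3 are 10.8%, 17.9% and 33.1%.

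**4. The other direction**

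Let 40% of intervention enrolees carry the factor, with k = 2. Under no effect, p = 0.1538 × 1.40 = 0.2154 and the one-sided error falls to 2.3%. If the planned reduction is real (20% to 12%, a ratio of 0.6), the observed intervention risk becomes 0.6 × 0.2154 = 12.9%. Power at the effective size of 167.9 per arm, by the same formula, falls from about 64% to about 54%. The bias then hides a benefit.

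**The case against.** The strongest reply is that this is a condensed article. Masking of recruiters and instructions to approach women consecutively often sit in the full protocol, and every cluster trial has this vulnerability. The invitation criteria in 2.8 are objective, and no selection among eligible women is described. Periodontists are blinded, which limits discretion in the oral exclusions. Screening is logged, baseline tables would show an imbalance, and a Cox model already adjusts for maternal age and other factors. The size of the bias is wholly assumed, and its direction is unknown.

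Much of this stands. A reader might infer three stronger things that the article does not say:

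- **That physicians take consent.** Section 2.8 has them suggest participation; it does not say who takes the signature.
- **That women know the arm when they decide.** One information sheet is mentioned, with no arm-specific version.
- **That recruiting physicians are told the arm.** The email goes to the principal investigator. That others learn it is an inference from the staff training and from delivery in the same clinic.

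Disclosure before the first invitation is likewise implied by the order of the text and not dated.

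The reply does not close the gap. The article itself fixes when and to whom the arm is disclosed and who invites women, and it confines blinding to later stages. Logs and baseline tables can reveal differential recruitment but cannot prevent it. The Cox covariates would remove only part of an imbalance in obesity or blood pressure.

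**Conclusion.** The point holds as a weakness of the stated process: recruitment could differ by arm, and the analysis would only partly repair it. The documents do not show that differential recruitment will occur, or in which direction. The error rates of about 10% and 14% are illustrations that rest on an assumed 10-point imbalance in a factor that doubles or triples risk. A weaker factor gives about 7%, and the opposite imbalance lowers the false-positive rate and costs power. Confidence is medium, because the recruiters' knowledge of the arm and the timing of disclosure are inferred. The change is worth making because most of it is inexpensive and the baseline data are already planned.

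**What to change.** 1. Require that every consecutive eligible woman be approached until the site quota is reached.
2. Complete eligibility, including the oral exclusions and the judgement on cooperation, and consent before the kit is handed over, with one information sheet stated to serve both arms.
3. Report numbers screened, eligible, invited and consented by arm, extending the log already kept.
4. Prespecify a cluster-adjusted primary comparison adjusted for maternal age, BMI and T1 blood pressure. Weight, height and blood pressure are already measured at T1 (2.6.2), and age is already a Cox covariate.
5. Where feasible, do not tell the inviting physicians the arm. The separation of implementers from data collectors in 2.9.2 helps here. Withholding it from the site principal investigator as well would conflict with the training arrangement in 2.9.1, so it is not asked for.

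Cost: items 1 to 3 are mainly wording and reporting, and item 4 adds a little analysis work and changes or supplements the stated main test. Item 5 gives only partial protection, because staff may guess the arm after the first few women.
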